#### Sample Size

The study will be powered to have an 80% chance of detecting a 40% reduction in incidence with statistical significance at the 5% level. It is assumed that study participants, in the absence of SMC, would experience 0.2 clinical episodes per child per high-transmission season (corresponding to the SMC round) of sufficient severity to present to a health facility [10]. The sample size calculation, based on the formula for a binary outcome superiority trial, shows that a sample of 654 eligible children (or 327 per arm) is required to provide sufficient statistical power. This multiplies to 818 under the assumption of a 20% loss to follow-up over the four cycles. Therefore, we aim to recruit a minimum of 800 eligible children (400 per arm).

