#### Data Analysis

Data will be analyzed using multivariate logistic regression with odds ratios estimated for the association between allocation to the intervention arm and (suspected and confirmed) malaria diagnosis at any point during the study period, converted to a percentage estimate of protective effect. To compensate for the lack of preintervention random allocation of participants to intervention or control groups, covariate adjustment will be made for potential confounders that may influence respondents’ odds of experiencing a clinically significant case of malaria. Covariates, measured at baseline, will include sex, age, parental education, and long-lasting insecticidal net use and all of these will be operationalized as categorical variables. Analyses will also use a multivariate Cox proportional hazards model with multiple Cox regression. *Failure* defined as a visit to a health facility for suspected malaria and/or a confirmed case of malaria and timing of this event based on the original date of health facility attendance during the study period and the estimated protective effect calculated.

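### The trial's sample size uses an episode rate of 0.2 per child as if it were the proportion of children with an episode, so the 80% power is overstated if children have repeat episodes

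*Protocol article*

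**What the plan says.** The Sample Size section of the nonrandomized controlled trial sets the aim: "The study will be powered to have an 80% chance of detecting a 40% reduction in incidence with statistical significance at the 5% level". The control-arm assumption is: "It is assumed that study participants, in the absence of SMC, would experience 0.2 clinical episodes per child per high-transmission season", counting episodes severe enough to bring the child to a health facility. The calculation is described as "based on the formula for a binary outcome superiority trial" and gives 654 evaluable children, 327 per arm. For attrition the section says: "This multiplies to 818 under the assumption of a 20% loss to follow-up over the four cycles". It then sets the recruitment target at a minimum of 800, 400 per arm.

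The Data Analysis section of the same component plans logistic regression of "malaria diagnosis at any point during the study period, converted to a percentage estimate of protective effect". That outcome is yes or no for each child. A Cox model for the time to such an event is also planned.

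**The concern.** The two planning inputs, episodes per child and a reduction in incidence, describe event rates. The formula and the logistic analysis need the proportion of children with at least one event in each arm. The protocol does not say that 0.2 is such a proportion, and it gives no distribution of episodes per child.

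The direction of the error is known. When some children have more than one episode, fewer than 20% of children account for a mean of 0.2 episodes. The control risk then falls below 0.20. If the 40% reduction applies to the rate, the absolute difference between the arms shrinks as well.

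Determining the protective effect of SPAQ where SP resistance is suspected is one of the study's two primary aims. At 69% power the chance of missing a true 40% reduction is about 31%, against the 20% that the protocol implies. A reader weighing a non-significant result needs the right figure.

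**Working it through.** **Inputs from the protocol (Sample Size).** Power 80%; 5% significance (sidedness not stated); 0.2 episodes per child; 40% reduction; 20% loss to follow-up; at least 800 recruited, 1:1.

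**Step 1: reproduce the plan's figure.** Treat 0.2 as a risk, so p1 = 0.20 and p2 = 0.6 × 0.20 = 0.12, two-sided.
- Unpooled: n = (1.960 + 0.842)² × (0.20×0.80 + 0.12×0.88) / 0.08² = 325.7, so 326 per arm.
- Pooled variance: 329 per arm.
- The stated 327 lies between these. A one-sided test (259) and a continuity-corrected formula (354) do not fit.
- Attrition: 654 / 0.8 = 817.5, so 818.

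The arithmetic is right for its inputs, and it shows that 0.2 episodes per child was entered as a risk of 0.20.

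**Step 2: evaluable children at the stated target.** 400 × 0.8 = 320 per arm, 640 in all, which is 14 fewer than 654. With 0.20 vs 0.12 at 320 per arm, the standard error is √[(0.1600 + 0.1056)/320] = 0.0288 and 0.08/0.0288 = 2.777. Power is Φ(2.777 − 1.960) = 79.3% (79.0% pooled). At 327 per arm it is 80.2% (79.8% pooled). Recruiting 800 in place of 818 therefore costs about 1 percentage point.

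**Step 3: take 0.2 as a rate.** The documents give no distribution, so a Poisson count is assumed here. The risk of at least one episode is 1 − exp(−rate):
- control: 1 − exp(−0.20) = 0.1813
- SMC: 1 − exp(−0.12) = 0.1131
- difference: 0.0682

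At 320 per arm the standard error is √[(0.1484 + 0.1003)/320] = 0.0279 and the ratio is 2.446. Power is Φ(2.446 − 1.960) = 68.7% (68.3% pooled). With no loss at all, 400 per arm would give 78%. For 80% power, 420 (unpooled) to 423 (pooled) evaluable per arm are needed.

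**Step 4: detectable effect under Poisson.** A 45% reduction gives a rate of 0.11 and a risk of 0.1042 under SMC. Power at 320 per arm is then 80.1%.

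**Step 5: other readings, all at 320 per arm.** The dispersion values are assumptions. The negative binomial risk is 1 − (1 + d×rate)^(−1/d), with variance equal to mean + d × mean².

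| Reading | Risks | Power |
|---|---|---|
| 0.2 is a proportion, 40% off the risk | 0.200 vs 0.120 | 79% |
| Poisson control risk, 40% off the risk | 0.181 vs 0.109 | 74% |
| 0.2 is a proportion, 40% off the underlying rate | 0.200 vs 0.125 | 73% |
| Cox model, hazard ratio 0.6, about 94 first events | – | 70% |
| Poisson, 40% off the rate | 0.181 vs 0.113 | 68–69% |
| Negative binomial, d = 0.5 | 0.174 vs 0.110 | 64% |
| Negative binomial, d = 1 | 0.167 vs 0.107 | 59% |
| Negative binomial, d = 2 | 0.155 vs 0.102 | 52% |

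None includes a design effect for the sampling of communities.

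**The case against.** The best defence is that 0.2 was meant as the proportion of children who present, as the formula uses it. The cited source is not available here, so this cannot be excluded. On that reading the calculation is sound and power at 800 is 79%. A reader might therefore infer from Step 3 that true power is 69%. The documents do not support that as a fact: it rests on a Poisson assumption that they do not make, and the readings tried run from 52% to 79%. This part of the objection stands.

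A reader might also infer that recruiting 800 instead of 818 causes the loss of power. It does not. It accounts for about 1 point, and 800 is worded as a minimum. It remains an inconsistency, because the stated target falls short of the stated requirement.

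The practical effect can also be called modest. Under Poisson the detectable reduction moves only from 40% to about 45%, and power is 89% for a 50% reduction and above 99% for 75%, roughly the effect that the Introduction cites for SMC elsewhere. A true rate of 0.27 would restore 80%. Children lost to follow-up can also contribute partial time to the Cox model. All this is fair. But the protocol chose 40% at a rate of 0.2 as its design point, in a setting where resistance could reduce the effect, and the power claim has to be true there.

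Finally, the protocol has no rule that a non-significant result means no protection. Misreading of a null result is thus a risk, not something that the plan prescribes.

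**Conclusion.** The concern holds in this form: a mean episode count and an incidence reduction are used as risks without saying so, while the analysed outcome is any diagnosis per child. If 0.2 is an episode rate, as written, and any child has a repeat episode, the 80% power is overstated. The size depends on what the documents leave open: about 68–69% with Poisson episodes, lower if episodes cluster within children (about 59% with dispersion 1), and about 79% if 0.2 is a proportion. These figures assume a two-sided 5% test, 320 evaluable per arm and no design effect. None of the readings tried reaches 80% at 800 recruited. The gap between 800 and 818 is secondary.

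**What to change.** In the Sample Size section, state the assumed proportion of children with at least one confirmed episode in each arm, with its support, and restate the power for 800 recruited and 20% loss:
- if 0.20 and 0.12 are those proportions, about 79%;
- if 0.2 is an episode rate, about 68–69% for a 40% reduction in the rate, with the Poisson assumption named, a note that overdispersion lowers it, and the detectable reduction given as about 45%.

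In either case, say that the figure is before any design effect. Also acknowledge that a target of 800 leaves 640 evaluable against the 654 required. No additional children are needed, and the only cost is a less favourable stated power.

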#### Primary Outcome

The primary outcome of this study will be visits to a health facility for suspected malaria by eligible children and confirmation of malaria diagnosis using an RDT during the 5-month study period, which includes a period of 28 days after the final administration of SPAQ.

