### Study Design

We will adopt a type 2 hybrid effectiveness-implementation study design that evaluates the effects of a clinical intervention on relevant outcomes while collecting information on implementation [29]. The hybrid effectiveness-implementation study design supports the pursuit of different lines of research simultaneously, which facilitates the more rapid translation and uptake of study findings for policy makers and implementers [29,30]. This study will use mixed methods to address the aforementioned objectives. Assessments of the protective effect of SPAQ, as delivered as part of SMC implementation, will provide evidence on whether this is appropriate in a region where SP resistance is suspected. Evaluating the implementation of SMC will generate knowledge on the feasibility and acceptability of this intervention in situ, including the challenges, barriers, and facilitators in the local context. Such findings can be useful to inform which intervention components are generalizable and which require local adaptation for other settings [31].

Four monthly cycles of SMC drugs will be distributed door-to-door to eligible children aged between 3 and 59 months by community distributors between November 2020 and February 2021 in 2 districts of Nampula Province. SMC tools and protocols used in Sahelian countries where the Malaria Consortium supports SMC delivery will be adapted to the context in Mozambique for this purpose. A third district will serve as a comparison district (the latter will receive standard malaria prevention, control, and case management). Data collection across the study components was conducted between October 2020 and May 2021 (Figure 3).

The methods are organized according to the study objective, described in more detail below, with an overview provided in Table 2 and Figure 3.

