**Figure 3 figure3:**
[figure not shown]
Timeline of seasonal malaria chemoprevention study objectives. Obj: Objective; RCT: randomized controlled trial; SMC: seasonal malaria chemoprevention; SPAQ: sulfadoxine-pyrimethamine and amodiaquine.

**Table 2 table2:** Overview of research objectives, methods, and sampling.

Objective	Method	Study population	Inclusion criteria	Exclusion criteria	Sample size (N=3320), n (%)
SPAQ^a^ resistance molecular marker monitoring	Quantitative: molecular analysis	Eligible children aged 3-59 months on the day 1 of the first SMC^b^ cycle	Aged 3-59 months attending the health facilities in study area with fever or history of fever in preceding 24 hours, with a positive malaria RDT^c^ and, with prior informed consent obtained from the parents or guardians	Presence of any signs or symptoms of severe malaria, refusal to participate	600 (18.07)
Nonrandomized controlled trial	Quantitative: nonrandomized controlled trial	Eligible children aged 3-59 months on the day 1 of the first SMC cycle	Eligible children, visited home for enrollment	Presence of a severe, chronic illness and a history of a significant adverse reaction to sulfadoxine-pyrimethamine or amodiaquine Refusal to participate	800 (24.09)
Assessment of impact of SMC on reported malaria morbidity indicators	Quantitative: DHIS2^d^ or SISMA^e^ data analysis	Data quality audit and morbidity analysis of all confirmed malaria cases reported in children aged less than 5 years in the 3 study districts from November 2020 to March or May 2021	HMIS^f^ data on health facility attendance for children aged 0-13 years (inclusive) will be extracted from health facility registers as full line listings, covering November 2020 to May 2021	Data from children aged >13 years or those falling outside the specified dates	26 health facilities in all 3 study districts
Process documentation of SMC adaptation	Qualitative: documentation of the adaptation process	N/A^g^	N/A	N/A	N/A
Feasibility and acceptability assessment	Qualitative: KIIs^h^ and FGDs^i^	Health workers implementing SMC Caregivers of children aged 3-59 months, community members, and community leaders Health workers SMC implementers Health officials and policy makers (district, provincial, and national)	Must fall into one of the study population’ categories, must consent to participate	Not categorized into one of the described study populations Refusal to participate	120 (3.61)

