### Nonrandomized Controlled Trial

#### Overview

A nonrandomized controlled trial will be conducted to determine whether the receipt of SPAQ is associated with a reduction in the odds of clinically significant malaria outcomes and to estimate the protective effect of SPAQ. There will be two arms: one (control arm) in the comparator district and the other in one of the SMC intervention districts. Communities will be randomly selected in both the intervention and control districts. Eligible children (aged 3-59 months at the first SMC cycle) will be recruited through random selection. Exclusion criteria include the presence of a severe, chronic illness and a history of a significant adverse reaction to SP or AQ. Selected children will be treated appropriately and retained during the trial. In the control district, communities bordering the intervention district will be avoided because of potential unintended *leakage* of SPAQ across the district boundary.

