#### Recruitment and Data Collection

Households will be randomly sampled from selected communities in both the control and intervention arms and 1 eligible child recruited at random in each household. A short baseline questionnaire will be administered to collect individual data on each child and to confirm their eligibility after the caregivers provided their consent. In the intervention arm, the questionnaire will be administered before the intake of SPAQ for SMC. The primary end point will be recorded through passive surveillance by study clinicians in both the intervention and comparator areas during the 4-month study period. Children recruited into the study presenting at clinics will be identified using information on SMC record cards, on which a child’s information and SMC doses are recorded, and data on health facility visits including suspected malaria cases and results of RDTs will be matched to baseline questionnaire data to build a database for analysis.

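### The trial endpoint depends on an unblinded judgement that malaria is suspected, so attendance, suspicion and testing can differ by arm and bias the protective effect in either direction.

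*Protocol article*

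**What the plan says.** All sections are in the Protocol article. Under Nonrandomized Controlled Trial, Primary Outcome, an event is "visits to a health facility for suspected malaria by eligible children and confirmation of malaria diagnosis using an RDT". Recruitment and Data Collection adds: "The primary end point will be recorded through passive surveillance by study clinicians in both the intervention and comparator areas". It also says: "Children recruited into the study presenting at clinics will be identified using information on SMC record cards". These cards hold the child's information and SMC doses, and the visit data are then matched to the baseline questionnaire.

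The Overview of the trial places the arms as "one (control arm) in the comparator district and the other in one of the SMC intervention districts", so arm and district coincide. Study Design says of the comparison district that "the latter will receive standard malaria prevention, control, and case management". No placebo or blinding is described.

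Data Analysis converts odds ratios from a logistic model into a percentage protective effect, adjusting for sex, age, parental education and net use. It adds a Cox model whose failure is "defined as a visit to a health facility for suspected malaria and/or a confirmed case of malaria".

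For the molecular marker survey, Table 2 uses an explicit entry criterion: "fever or history of fever in preceding 24 hours, with a positive malaria RDT".

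**The concern.** An RDT result is fairly objective, but an RDT-confirmed endpoint is objective only if the chance of being tested does not depend on arm. Here three unblinded steps come before the result: the caregiver decides to attend, someone suspects malaria, and a test is done. An arm difference at any of these steps changes the count of confirmed cases without any drug effect.

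The Cox definition adds a second route. Because a suspected visit can be a failure without confirmation, unblinded suspicion can itself be an event.

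The trial asks whether SPAQ still protects where SP resistance is expected to be high. A modest true effect is possible there, and a modest ascertainment difference could change the answer.

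**Working it through.** **The plan's own figure.** The inputs, from Sample Size, are a control risk of 0.20, a 40% reduction (so 0.20 × 0.60 = 0.12), 5% significance (two-sided assumed) and 80% power. The two-proportion formula gives 326 per arm (unpooled variance) or 329 (pooled), against the stated 327. Inflating for 20% loss, 654/0.80 = 817.5, or 818, as stated. The sample size is sound and this point does not rest on it. Recruiting 400 per arm with 20% loss leaves 320 per arm.

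**Effect of unequal testing.** Assumptions not in the documents:
- Each child has at most one episode, with true risk 0.20 in the control arm.
- A fraction t_C of control episodes and t_S of SMC episodes is suspected and tested.
- The RDT is perfect.

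The observed risks are q_C = 0.20 × t_C and q_S = 0.20 × (1 − e) × t_S, where e is the true risk reduction. The odds ratio is [q_S/(1 − q_S)] / [q_C/(1 − q_C)].

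*Complete testing, e = 0.40:* (0.12/0.88)/(0.20/0.80) = 0.136/0.250 = 0.545, so 1 − OR = 45%. This is the unbiased reference.

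*90% control, 80% SMC, e = 0:* q_C = 0.18, q_S = 0.16. OR = (0.16/0.84)/(0.18/0.82) = 0.1905/0.2195 = 0.87, so 13% spurious protection. On the risk scale, 1 − 0.16/0.18 = 11%.

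*90% control, 80% SMC, e = 0.40:* q_S = 0.12 × 0.80 = 0.096. OR = (0.096/0.904)/0.2195 = 0.1062/0.2195 = 0.484, so 52% instead of 45%. On the risk scale, 47% instead of 40%.

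*90% control, 85% SMC, e = 0:* q_S = 0.17. OR = (0.17/0.83)/0.2195 = 0.2048/0.2195 = 0.933, so 7% spurious protection.

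*Reverse gap, 80% control, 90% SMC, e = 0.40:* q_C = 0.16, q_S = 0.108. OR = (0.108/0.892)/(0.16/0.84) = 0.1211/0.1905 = 0.636, so 36% instead of 45%.

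**Consequence for the test.** With 320 per arm and no drug effect, observed risks of 0.18 and 0.16 give about a 10% chance of a significant false benefit, against a nominal 2.5% in that direction. With a true 40% reduction, the reverse gap leaves about 49% power, against 79% with complete testing.

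**The case against.** Four objections have substance.

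1. *The article may simply omit the testing rule.* A condensed article can leave operational case definitions to the full protocol, which Availability of Data and Materials says can be requested. Nothing states that testing differs by arm. This limits the point: it cannot be said that testing will differ. But the endpoint that begins with suspicion, the dose card as identifier and the and/or failure definition are stated in this text.

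2. *A reader might infer that clinicians decide whether to test with the dose card in hand.* The documents do not support that. The card is mentioned as the means of identifying children and linking records, and the order of card reading and testing is not given. Nor is it said whose suspicion counts; it may be the caregiver's reason for attending. The concern does not need either reading, because the district alone can reveal the arm to both.

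3. *A reader might infer that the bias must favour SMC.* That is not supported either. Clinicians watching for SMC failure could test more in the intervention district. The working shows both directions.

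4. *An untested child can still be an event in the Cox model, and testing can be examined elsewhere.* Both are true. The and/or wording makes suspicion alone sufficient there, which is a further weakness and no protection. The routine-data component does extract line listings from all three districts, including whether a malaria test was performed. Those are not limited to enrolled children and are not linked to the trial analysis, but they are useful for a check.

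**Conclusion.** The point holds in this form. As written, attendance, suspicion and testing are unblinded and can depend on arm, and adjustment for sex, age, parental education and net use does not remove that. The direction is not known. The size rests entirely on assumed testing rates: gaps of 5 to 10 percentage points give about 7% to 13% spurious protection on the 1 − OR scale used in Data Analysis, and the 10-point gap moves a true 40% risk reduction from 45% to 52% in one direction or to 36% in the other. The documents do not show that such gaps will occur. The change is worth making before data collection where possible, because the protocol already holds a more objective criterion.

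**What to change.** 1. In Primary Outcome and in Recruitment and Data Collection, use the Table 2 criterion (fever, or history of fever in the preceding 24 hours) in both arms as the trigger for an RDT for outcome ascertainment. Apply it to every enrolled child who attends, whatever the SMC card shows, and make RDT-positive among these the primary outcome. This concerns how events are counted, not how children are treated.

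2. In Data Analysis, define the Cox failure as the RDT-confirmed visit, dated at attendance. Suspicion alone should not be a failure.

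3. Report RDT-negative suspected-malaria visits by arm from the visit data that Recruitment and Data Collection already describes. Compare the share of attendances tested by district and age from the routine-data line listings. A clear difference would point to arm-related attendance or testing, though districts may also differ for other reasons.

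Cost: some additional RDTs, fever recorded at every study visit (the text does not show that it is recorded where malaria was not suspected), and one table. A reported history of fever and the decision to attend remain unblinded; unblinded care seeking is checked, not removed. The article states that data collection began in October 2020. If it is complete, item 1 can no longer be applied and only items 2 and 3 remain.
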